#### CMRI analyses

CMRI analyses are carried out in an independent core lab blinded for additional patient information and results. The image quality of all acquired images is scored qualitatively using a scale from 1 to 3. Scores defined as 1 indicate a good image quality with no artifacts; scores defined as 2 indicate a moderate image quality, which is acceptable for clinical or research diagnosis; and scores defined as 3 indicate poor image quality, and diagnosis is impossible due to severe artifacts. Poor image quality (score 3, non-diagnostic) is considered abnormal.

The images are also evaluated qualitatively with a binary outcome (normal/abnormal) based on the perfusion analyses, presence of wall motion abnormalities, or low ejection fraction. Perfusion analyses at stress and rest are scored as significant, insignificant, or no defect based on the 17-segment model of the American Heart Association. Significant perfusion defects are defined as subendocardial or transmural signal changes in ≥ 2 contiguous segments, corresponding to approximately 6–12 % of the myocardium.

The presence of irreversible defects is considered abnormal if signal changes appear in ≥ 2 contiguous segments on the viability scans. Evidence of regional wall motion abnormalities is scored using a scale from 1 to 4: 1 is normal, 2 is hypokinetic, 3 is akinetic, and 4 is dyskinetic.

A hybrid imaging analysis with combined information from CCTA and CMRI blinded from the result of the ICA are performed after the initial analysis.

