#### Image analysis

Image analysis will be conducted in Cedar Sinai AutoQuant software in Phillips Intellispace Portal v6.0.3.12200 in an independent core lab by the same nuclear physician, who is blinded to additional patient information and results. The quality of the stress and rest images will be evaluated semi-quantitatively on a visual scale from 1 to 3. Scores defined as 1 represent a good image quality with no artifacts; scores defined as 2 indicate moderate image quality, acceptable for clinical or research diagnosis; and scores defined as 3 are consistent with poor image quality, and diagnosing is impossible due to severe artifacts. The MPS images are assessed using a 17-segment model. For each segment, perfusion defects are scored automatically by the software and adjusted visually on a five-point scoring system (0 is normal, and 4 is the absence of tracer uptake). The scores from the stress and rest images are summed, and a summed stress score (SSS), summed rest score (SRS), and summed difference score (SDS) will be produced. The images will also be evaluated qualitatively with a binary outcome (normal/abnormal). An abnormal MPS scan is defined as (1) an SDS ≥ 43? involving ≥ 2 contiguous segments corresponding to approximately 10 % (reversible ischemia); (2) an SRS ≥ 43? involving ≥ 2 contiguous segments (irreversible ischemia); (3) a combination of reversible and irreversible ischemia involving ≥ 2 contiguous segments (mixed ischemia). Poor image quality (score 3, non-diagnostic) is considered abnormal (Fig. 2).

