#### First objective

The first objective of the study is to assess the diagnostic accuracy of MPS and CMRI in two comparable samples using hemodynamic significant obstructive CAD at ICA-FFR as the reference standard. The diagnostic performance will be evaluated on a patient level by sensitivity, specificity, predictive values, and likelihood ratios as well as by a binary abnormal/normal test outcome. The sensitivity and specificity of the MPS and CMRI are being compared by Chi^2^ test.

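### Wall motion and ejection fraction can make a CMRI scan abnormal but not an MPS scan, so a difference on the Chi² comparison cannot be attributed to the modality alone

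*Protocol article*

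**What the plan says.** All references are to the protocol article.

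**CMRI (CMRI analyses).** The core lab gives a binary normal/abnormal reading "based on the perfusion analyses, presence of wall motion abnormalities, or low ejection fraction". The perfusion component is specific: "Significant perfusion defects are defined as subendocardial or transmural signal changes in ≥ 2 contiguous segments". Scar counts as well: "The presence of irreversible defects is considered abnormal if signal changes appear in ≥ 2 contiguous segments on the viability scans".

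**MPS (Image analysis).** The segmental scoring concerns perfusion: "For each segment, perfusion defects are scored automatically by the software and adjusted visually on a five-point scoring system". The definition then opens "An abnormal MPS scan is defined as (1) an SDS" and lists three routes to an abnormal scan: a reversible defect, an irreversible defect, or a mixture of the two, each over at least two contiguous segments. Neither wall motion nor ejection fraction is among them.

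**Non-diagnostic scans.** The rule is the same in both arms: "Poor image quality (score 3, non-diagnostic) is considered abnormal".

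**Comparison (First objective).** "The sensitivity and specificity of the MPS and CMRI are being compared" by a Chi² test, with hemodynamically significant obstruction at ICA-FFR as the reference standard. The Discussion calls this a head-to-head comparison of the two modalities. The abstract, the Discussion and the Perspective describe the second test as a perfusion examination.

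**The concern.** The two arms apply different rules for calling a scan positive. CMRI has two routes to abnormal that MPS lacks, and neither route measures what the reference standard measures, namely FFR or high-grade stenosis. Take a patient with normal perfusion, no scar, no obstruction at ICA-FFR and a low ejection fraction from another cause. On the plain reading, that patient is a false positive if randomised to CMRI and a true negative if randomised to MPS. In the other direction, a patient with obstruction whose perfusion looks normal but whose wall motion does not is a true positive under CMRI and a false negative under MPS.

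MPS technique does not force this difference. The acquisition is gated in eight frames (MPS image acquisition), suspected motion abnormality is one trigger for a rest study (MPS protocol), and function is listed among the recorded items for both modalities (Data). What is at stake is how the between-modality test is interpreted: a significant result could come from the modality, from the wider rule, or from both.

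**Working it through.** **Inputs from the article.** Assumed sensitivity and specificity 0.83 for both modalities, 300 randomised patients, 95% CI half-width 0.10 (Sample size); 1:1 allocation (Randomisation and blinding procedure); two-sided 0.05 (Second objective).

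**Inputs the article does not give, so assumed.**
- p: share of perfusion-normal patients without obstruction who have a wall motion abnormality or low ejection fraction.
- a: the same share among perfusion-normal patients with obstruction.
- Prevalence of obstruction among randomised patients.

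**Step 1. The rules side by side.**

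| Component | CMRI | MPS |
|---|---|---|
| Perfusion defect, at least 2 contiguous segments | counts | counts |
| Irreversible defect, at least 2 contiguous segments | counts (viability scan) | counts (rest score) |
| Non-diagnostic quality | abnormal | abnormal |
| Wall motion abnormality | counts | not listed |
| Low ejection fraction | counts | not listed |

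The asymmetry is confined to the last two rows. The numeric score cut-off for MPS is not legible in the text at hand; nothing here depends on it.

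**Step 2. Direction.** Adding a route with *or* can only add positives:

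- specificity with the added routes = specificity × (1 − p)
- sensitivity with the added routes = 1 − (1 − sensitivity) × (1 − a)

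So specificity falls or stays, and sensitivity rises or stays.

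**Step 3. The plan's own figure.** n = 1.96² × 0.83 × 0.17 / 0.10² = 54.2, so 55 patients with and 55 without obstruction per arm. A total of 300 follows at a prevalence of about 36.7% (2 × 55 / 0.367 ≈ 300). No prevalence is stated, so 300 is compatible with the inputs but not uniquely reproduced. It serves here only for scale: 150 per arm has about 95 patients without obstruction at 36.7%, and 75 at 50%.

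**Step 4. Size if 0.83 is the perfusion-only specificity in both arms.** The chance that the test declares CMRI specificity lower is Φ[(d − 1.96·SE₀)/SE₁], where d is the gap, SE₀ uses the pooled proportion and SE₁ the separate ones. With no gap it is 2.5%, half of the two-sided 5%.

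| p (assumed) | CMRI specificity | Gap to 0.83 | Declared lower, 95 per arm | Declared lower, 75 per arm |
|---|---|---|---|---|
| 0% | 0.83 | 0 | 2.5% | 2.5% |
| 5% | 0.83 × 0.95 = 0.79 | 4 points | 11% | 9% |
| 10% | 0.83 × 0.90 = 0.75 | 8 points | 29% | 24% |

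For sensitivity, 1 − 0.17 × (1 − a) gives 0.83 at a = 0%, 0.86 at 20%, 0.88 at 30% and 0.92 at 50%.

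**Step 5. Size if 0.83 already describes the composite CMRI reading.** Perfusion-only specificity would then be 0.83 / 0.95 = 0.87 at p = 5%, or 0.83 / 0.90 = 0.92 at p = 10%. The test would compare 0.83 with 0.83 and miss a perfusion-specificity gap of 4 or 9 points. The rule can hide a difference as well as create one.

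**The case against.** The strongest reply is that the positivity rule is part of the index test. CMRI is acquired here as a multiparametric examination covering morphology, function, perfusion and viability, and comparing each modality as it is read is a legitimate design. That stands, and so does its consequence: each arm's sensitivity and specificity are valid for the test as defined, and the sample size rests on the precision of those separate estimates. What it does not do is let the Chi² result speak for the modality alone. The article does not say that it intends a comparison of full readings, and MPS does not get one, since its gated function is left out.

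A reader might infer more than the document supports:

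- **That a 4 to 8 point distortion is established.** It is not. The 5% and 10% are assumptions, p may be near zero in a low-to-intermediate-risk population, and the article does not say whether 0.83 refers to perfusion alone.
- **That the rule favours CMRI.** It pushes sensitivity and specificity in opposite directions.
- **That the missing ejection-fraction cut-off and wall-motion extent are defects.** A condensed article commonly leaves such reading criteria to the full protocol. Supplying them would not remove the asymmetry.
- **That other heart disease is wholly unrestricted.** Table 1 excludes critical aortic stenosis and advanced AV block as adenosine contraindications. It does not name cardiomyopathy or reduced ejection fraction.

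The CMRI reading is also called qualitative, and no algorithm is printed. That one component suffices is the plain reading, not a stated formula.

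**Conclusion.** The point holds for the between-modality comparison only. Wall motion and ejection fraction enter the CMRI result and not the MPS result, so a difference, or the absence of one, on the Chi² test cannot be attributed to the modality alone. The direction follows from the word or: CMRI sensitivity up or unchanged, CMRI specificity down or unchanged. The size cannot be derived from the article. For assumed shares of 0% to 10%, and with 0.83 taken as perfusion-only specificity, CMRI specificity runs from 0.83 to 0.75, set against a planned precision of ±10 points. The article does not support calling the CMRI definition wrong, or either arm's own accuracy estimate biased.

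**What to change.** State that the Chi² comparison of MPS and CMRI uses matched criteria. For CMRI, abnormal would mean a significant stress perfusion defect and/or an irreversible defect on the viability scan, each in at least two contiguous segments, with non-diagnostic scans abnormal as in both arms now. Report the CMRI composite including wall motion and ejection fraction beside it, labelled as the full multiparametric reading.

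At minimum, keep the composite and prespecify the perfusion/viability-only CMRI result as a sensitivity analysis of the comparison. As 226 patients had been randomised by September 2015 (Trial status), the choice should be dated and made before the readings are analysed against ICA-FFR.

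Add a matching functional definition for MPS only if the recorded gated function data allow it without new reading. The Image analysis section describes no wall-motion or ejection-fraction scoring for MPS, so this part may not be free.

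Cost: one extra analysis from items that already have their own CMRI criteria, with no new scans or patients. The matched comparison does not use all the CMRI information. The match is also one of construct rather than of scale, since MPS uses summed scores and CMRI a three-level perfusion grade.

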### Invasive coronary angiography-fractional flow reserve (ICA-FFR) examination

#### Patient preparation

The ICA examination and the FFR assessments are performed according to present clinical guidelines. The ICA examinations are all conducted at Aarhus University Hospital, Aarhus, Denmark, approximately 4 weeks after referral to CCTA. The ICA is performed though the radial or femoral artery route. Heparin 5000 IE is administered when radial access is used, and 200 μg of nitroglycerine is given intra-coronary after the first angiographic projections.

#### Imaging protocol

All stenoses are visually assessed, and all stenoses above 30 % in vessels with a reference diameter above 2 mm are examined, with at least two projections at least 30 degrees apart revolving around the axis of the vessels. The overlap of vessels is avoided if possible. Angiography is recorded at a time resolution of 15 frames per second (fps).

FFR measurements are performed in all coronary segments with a diameter > 2 mm where ICA shows the presence of stenosis with a diameter ≥ 30 % by visual assessment. The position of the FFR wire is documented angiographically. FFR is measured using a pressure wire (Aeris, St. Jude Medical, Minnetonka, MN, USA) during continuous recording of the pressure curves. Hyperaemia is induced by an intravenous adenosine infusion of a 1 mg/mL concentration of adenosine at 140 μg/L/min. The infusion rate is increased to 200 μg/L/min if a stable FFR value is not achieved. Routine checks are made to ensure that ‘drift’ does not occur after FFR recordings. If the drift value exceeds 1.04 or is below 0.96, the FFR-measurement is repeated. Furthermore, all severe stenoses (> 90 %) in vessels with a reference diameter above 2 mm where there is no immediate indication of treatment, FFR is not possible or not attempted, are noted.

#### Imaging analysis

All evaluations are conducted with assessors blinded to the patient’s CAD score, MPS, or CMRI examinations.

Hemodynamic significant obstructive CAD is defined as FFR ≤ 0.80, or as high-grade stenosis (> 90 % diameter stenosis) by visual assessment in a vessel ≥ 2.0 mm in diameter. If FFR is indicated in a vessel ≥ 2.0 mm but not technically possible, then QCA-based stenosis will be used with a cut-off of ≥ 50 % diameter reduction, which defines an anatomically significant obstructive CAD. The 2D QCA is performed in an independent core lab (ClinFact, Leiden, The Netherlands) using QAngioXA 7.3 QCA software.

### Follow-up

The cohort is followed for 10 years after the CCTA examination. Data are extracted from the Civil Registration System (CRS) and National Patient Registry (NPR) by obtaining diagnosis of CAD including acute coronary syndrome, treatment with PCI/CABG, and causes of death. Cases are verified through electronic medical records that include biochemistry and medication as well as the results of diagnostic examinations.

### Data collection and recordings

All study data are recorded in a secure web-based electronic case record form (eCRF) that enables logging of all data entries (Biostata, Birkerød, Denmark). The CAD score measurement, patient interview, and blood samples are obtained by trained study nurses.

All investigators have access to the eCRF. During the study period, the monitoring of 100 % of the proxy authorizations and informed consent forms and 20 % of the data for biochemistry, Agatston score, comorbidity, and adverse events is conducted by an external contract research organization (Klifo, Glostrup, Denmark). The manuscript has been written following the ‘Standard Protocol Items: Recommendations for Interventional Trials’ and an additional file has been added listing each paragraph and its location in the manuscript (see Additional file 1).

### Randomisation and blinding procedure

Patients are randomised using a randomisation module in the eCRF. An external data manager is responsible for the eCRF, including the randomisation module (Biostata, Birkerød, Denmark). A random allocation sequence is created using a standard computerized random-number generator. The cardiologist analysing the CCTA randomises patients when obstructive CAD is suspected on CCTA. Randomisation is conducted without stratification and in a 1:1 ratio to either MPS or CMRI. The randomisation is open to all investigators and all patients. The physicians performing ICA-FFR are blinded to the results of the MPS or CMRI.

### Data

The following data will be collected during the project and registered in a dedicated eCRF:Demography—age, sex, and ethnical originCo-morbidityPrevious ischemic disease—stable angina pectoris, stroke, and peripheral arterial diseaseRisk factors for ischemic heart disease—genetic disposition, diabetes mellitus, hypertension and hypercholesterolemia, blood pressure, heart rate, weight, height, and smoking statusSymptoms—typical, atypical, or unspecific chest pain, New York Heart Association (NYHA) functional class, and Canadian Cardiovascular Society (CCS) score system of angina pectorisEcho—left ventricle ejection fraction (LVEF) and significant valve diseaseCCTA—scan quality, Agatston calcium score, anatomy, plaque type, and degree of stenosis and radiation exposureCAD score—registration of the CAD score, recording time, and positioning of the deviceMPS and CMRI—Scan quality, function, and perfusion defectsICA-FFR—data concerning anatomy, localization of stenosis, visual evaluation of stenosis, QCA measurements, FFR measurements, and whether treatment by PCI or CABG is performedFollow-up—cardiovascular events as well as possible cardiovascular or other causes of deathAdverse Events (AE)—all adverse events occurring in the study period are registered

### Endpoints and statistical analysis

Data analysis and reporting will follow the Standards for Reporting of Diagnostic Accuracy (STARD) guidelines and all demographic and baseline characteristics will be presented and analyzed using appropriate statistical methods.

#### First objective

The first objective of the study is to assess the diagnostic accuracy of MPS and CMRI in two comparable samples using hemodynamic significant obstructive CAD at ICA-FFR as the reference standard. The diagnostic performance will be evaluated on a patient level by sensitivity, specificity, predictive values, and likelihood ratios as well as by a binary abnormal/normal test outcome. The sensitivity and specificity of the MPS and CMRI are being compared by Chi^2^ test.

#### Second objective

The secondary objective is to evaluate the diagnostic precision of the CAD score using anatomical significant obstructive CAD at CCTA and ICA-QCA as the reference standard. The diagnostic performance will be evaluated on a patient level as the area under curve receiver operating characteristics (ROC-AUC) with the CAD score as a continuous variable. The CAD score is dichotomized with a positive value above 20, 25, and 30, respectively, and performance is reported with sensitivity, specificity, positive predicative value, negative predicative value, and diagnostic accuracy. In risk stratification the CADScor system operates with three intervals in CAD: < 20, 20–30, and >30 for low, intermediate and high risk, respectively.

Secondarily, the same calculations are made using hemodynamic significant obstructive CAD with ICA-FFR as the reference standard. Comparisons between subgroups are evaluated with ROC-AUC regression analysis. A comparison of the CAD score and MPS or CMRI is evaluated with the McNemars test of sensitivity and specificity at a CAD-score cut-off of 20, 25, and 30.

For all statistical analyses, a two-tailed *p* value < 0.05 was considered statistically significant, and 95 % confidence intervals are being reported when appropriate. Statistical analysis is performed using dedicated statistical software (STATA 13, StataCorp, College Station, TX, USA)

### Sample size

On the basis of previous data, we assumed a sensitivity and specificity of 0.83 for diagnosing obstructive CAD for both MPS and CMRI in patients referred to further examinations after CCTA [15, 17, 22, 36]. Based on these assumptions, a final randomised study cohort of 300 patients is required for a minimum of 10 % absolute precision on both sides (half width of the 95 % confidence interval (CI)) of the expected sensitivity and specificity for both MPS and CMRI. A minimum of 300 patients are needed to achieve sufficient power in the randomised study. To establish this study cohort, we estimate that a primary cohort of approximately 2,000 patients referred to CCTA is needed based on the assumption that 15–20 % of patients need further testing after CCTA.

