Cardiac magnetic resonance imaging (CMRI) offers many advantages such as no radiation exposure and high image resolution [15–20]. A lack of scanner capacity and expertise are often mentioned as limitations. Myocardial perfusion scintigraphy (MPS) is an established perfusion test; however, disadvantages such as radiation and low sensitivity are reported as well as a balanced reduction in blood flow to the myocardium in three-vessel disease [21–24]. Many studies assessing the diagnostic accuracy of CMRI and MPS have used ICA diameter stenosis as a reference standard [16, 18[20, 22], which has been shown to be inaccurate in assessing the functional significance of a coronary stenosis compared to ICA-FFR [3].

A meta-analysis on MPS found an average sensitivity of 84 % for women and 89 % for men and a specificity of 78 % for women and 71 % for men using invasive coronary angiography– quantitative coronary angiography (ICA-QCA) as a reference standard [25]. For CMRI, a meta-analysis of studies performed with ICA-FFR as the reference found an average sensitivity of 90 % and a specificity of 87 % [17].

The CADScor System (Acarix A/S, Denmark) is a newly developed technology, which automatically analyses sounds from the heart and extracts multiple acoustic features related to turbulent blood flow, which emerges in a coronary segment with stenosis, and other heart sounds characteristic to CAD [26–29]. Based on these characteristics, the system calculates a score. This score can potentially be used for risk stratification prior to CCTA and in diagnosing CAD [29].

The first objective of the present study is to determine the precision of MPS and CMRI as secondary examinations after CCTA when significant stenosis cannot be excluded.

Our second objective is to examine the diagnostic precision of the CAD score in patients with a low to intermediate risk of CAD and who have been referred to a primary examination by CCTA.

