## Discussion

The use of CCTA has proven to be a valid tool for ruling out CAD [6–9] in patients with a low to intermediate pre-test likelihood of CAD. However, the low positive predictive value of CCTA causes ‘unnecessary’ downstream ICA examinations in the sense that no revascularization is required. The need for more specific strategies for non-invasive diagnostic work-up of patients with suspected CAD was demonstrated in a large study comprising 398,978 patients where elective cardiac catheterization showed obstructive CAD in only 38 % of these patients [37]. The Dan-NICAD study aim to test the idea that more patients could potentially avoid unnecessary ICAs by performing a secondary perfusion-imaging test in patients where obstructive CAD could not be excluded with the CCTA. In prior studies looking at low to intermediate pre-test populations, approximately 70 % of the patients did not have obstructive CAD on CCTA [11]. Patients in the Dan-NICAD study in whom obstructive CAD is not excluded by CCTA will be randomised 1:1 to either MPS or CMRI with ICA-FFR as a reference standard for a head-to-head comparison of the diagnostic accuracy of these two modalities.

Several other studies have tested the accuracy of these two techniques. In the CE-MARC study [15], 752 patients with intermediate to high pre-test risks of obstructive CAD underwent both MPS and CMRI with ICA-QCA as a reference standard. The study showed both higher sensitivity and specificity of CMRI compared to MPS. The MR-IMPACT study [38] also made a head-to-head comparison of the two techniques and showed superiority of CMRI. Here, the patients were highly selected. Patients had either undergone an ICA (positive or negative) or had a positive MPS and were scheduled for ICA. Both studies used ICA-QCA, a reference standard proven not to be ideal [3], as it compares functional tests with an anatomical test. ICA-QCA is shown to overestimate the severity of CAD compared to FFR [3]. The MARCC study [11], with a population of low-to intermediate pre-test probability, tested the combined use of CCTA and CMRI for the diagnostic evaluation of patients with suspected CAD using ICA-FFR as a reference standard when disease was suspected on either CCTA or CMRI. The study showed improved specificity and diagnostic accuracy using a combined set-up.

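### The protocol credits 300 patients with sufficient power, but that number was derived only for per-arm precision and no assumption supports power for the planned Chi² comparison of MPS with CMRI

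*Protocol article*

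**What the plan says.** The Sample size section sets the assumption: "we assumed a sensitivity and specificity of 0.83 for diagnosing obstructive CAD for both MPS and CMRI". From it the section concludes that "a final randomised study cohort of 300 patients is required for a minimum of 10 % absolute precision on both sides", meaning the half-width of a 95% confidence interval for each test's sensitivity and specificity. The next sentence is "A minimum of 300 patients are needed to achieve sufficient power in the randomised study". It gives no hypothesis, difference, margin or power level.

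Under First objective the two randomised arms are compared: "The sensitivity and specificity of the MPS and CMRI are being compared by Chi^2^ test". Under Second objective the general rule is "For all statistical analyses, a two-tailed *p* value < 0.05 was considered statistically significant". The Discussion says that patients are randomised "for a head-to-head comparison of the diagnostic accuracy of these two modalities".

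The Background gives the only accuracy figures in the article. A meta-analysis of MPS against quantitative angiography "found an average sensitivity of 84 % for women and 89 % for men", with specificity of 78% and 71% respectively. A meta-analysis of CMRI against FFR found 90% sensitivity and 87% specificity.

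**The concern.** Precision for one proportion and power to separate two proportions are different properties. The first is what 300 was derived for; the second is what the next sentence claims. Because both tests are assumed to perform identically, the sizing contains no difference against which power could be defined.

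The sentence matters because the protocol does plan a hypothesis test between the arms. Sensitivity is compared among FFR-positive patients only and specificity among FFR-negative patients only, so each test uses a fraction of the 150 per arm. If a Chi² result is non-significant in a trial described as adequately powered, readers may conclude that the two tests are equally accurate when the data could not settle the question.

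**Working it through.** **Inputs.** From the protocol: 300 randomised 1:1, so 150 per arm; 0.83 for both tests; two-sided 5% level; the Background accuracy figures. Assumed: prevalence of FFR-positive disease among randomised patients. The protocol gives none. I use 38%, the share with obstructive disease in the large elective catheterisation study cited in the Discussion. That is a different population, so I also show 20–60%. At 38% there are 0.38 × 150 = 57 positives and 93 negatives per arm.

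**The protocol's own figure.** n = 1.96² × 0.83 × 0.17 / 0.10² = 54.2, so 55 positives and 55 negatives per arm. A total of 300 follows if prevalence is 55/150 = 36.7%. At 38%, 300 gives half-widths of 9.8 points (sensitivity) and 7.6 points (specificity). The target is met for prevalence of about 36% to 64% (54.2/150 = 0.361 and its complement). At 30% the sensitivity half-width is 11.0 points. The precision rationale is therefore plausible, though it depends on an unstated prevalence.

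**Power under the stated assumption.** With 0.83 in both arms the true difference is zero, and the test rejects with probability 5% whatever the sample size.

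**Detectable difference at 80% power.** Normal approximation to the Chi² test, pooled variance under the null:
- Sensitivity, 57 per arm: 23.6 points down (0.83 to about 0.59) or 15.2 up (to about 0.98).
- Specificity, 93 per arm: 17.9 points down (to about 0.65) or 12.7 up (to about 0.96).

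**Power at the Background figures, as illustrations.** For sensitivity 0.90 v 0.84 with 57 per arm:
- Critical difference: 1.96 × √(2 × 0.87 × 0.13 / 57) = 0.1235.
- Standard error under the alternative: √((0.90 × 0.10 + 0.84 × 0.16)/57) = 0.0627.
- Power: Φ((0.06 − 0.1235)/0.0627) + Φ((−0.06 − 0.1235)/0.0627) = 0.156 + 0.002 = 0.158.

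| Contrast (CMRI v MPS) | Power at 38% prevalence | Over 20–60% prevalence |
|---|---|---|
| Sensitivity 0.90 v 0.84 | 16% | 10–22% |
| Sensitivity 0.90 v 0.89 | 5% | 5–6% |
| Specificity 0.87 v 0.78 | 36% | 25–45% |
| Specificity 0.87 v 0.71 | 77% | 58–87% |

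Exact enumeration of the uncorrected Chi² test agrees within about one percentage point. For 0.90 v 0.84, 80% power needs 492 FFR-positive patients per arm. Even if all 150 per arm were FFR-positive, power would be 34%.

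**Precision of the difference.** Half-width = 1.96 × √(2 × 0.83 × 0.17 / n): 13.8 points for sensitivity (n = 57) and 10.8 points for specificity (n = 93).

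**The case against.** The strongest reply is that the disputed sentence is loose wording. The preceding sentence discloses the precision basis, the first objective is to assess each test's accuracy, and 300 is compatible with the precision target over a wide range of prevalence. That stands as a defence of the number: nothing here shows that 300 is wrong. It does not rescue the power claim, because a between-arm significance test is planned and a reader will attach the sentence to it.

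Specificity, which is closest to the aim of avoiding unnecessary invasive angiography, fares much better than sensitivity. A reader might infer that a non-significant comparison is likely even if CMRI is truly better. The documents do not support that in general. Specificity of 0.87 v 0.71 has 77% power at 38% prevalence and passes 80% at 30% or below. The two tests use different patients, so at the men's figures the chance that at least one is significant is 1 − (1 − 0.768)(1 − 0.053) = 78%. At the women's figures it is 1 − (1 − 0.364)(1 − 0.158) = 46%.

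The effect sizes are also weak as planning values. The MPS figures use quantitative angiography as reference and the CMRI figures use FFR, so the gaps between them are not the differences expected in this trial. The 0.90 v 0.89 contrast is a single point that no trial of this kind would be sized for. This objection stands, which is why the detectable differences from 0.83 carry the argument.

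Nor is the Chi² test the only test involving randomised patients: McNemar tests of the CAD score against MPS or CMRI are planned too. Finally, the protocol nowhere says that non-significance will be read as equivalence, and it promises confidence intervals where appropriate. The risk lies in how the power sentence may be used.

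**Conclusion.** The concern holds for the power sentence and not for the sample size. The stated inputs give a precision calculation with a zero assumed difference, and nothing in the document supports power for the between-arm comparison.

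For sensitivity the shortfall is large. The detectable difference is about 24 points down or 15 up from 0.83 at 38% prevalence, and power for a 6-point gap stays at or below 22% for any prevalence from 20% to 60%. For specificity it is moderate and depends on the true difference: about 18 points down or 13 up, with power from 25% to 87% over the two illustrative contrasts and the same prevalence range. These sizes rest on 150 evaluable patients per arm and on an assumed prevalence; the absence of a stated difference, margin or power level does not.

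**What to change.** Replace the power sentence with a statement that 300 is chosen for the precision of each test's sensitivity and specificity and not for the comparison between tests, and give the prevalence of FFR-positive disease assumed. Under First objective, add that the between-arm differences in sensitivity and specificity will be reported with 95% confidence intervals beside the Chi² p values, with expected half-widths of about 14 and 11 points at 38% prevalence. Add that a non-significant Chi² result will not be interpreted as equal accuracy.

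The sample size, the conduct of the trial and the planned tests stay as they are. The cost is a few sentences, two extra intervals, and a less favourable claim about what the comparison can show.
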